#### Secondary endpoints

Relative risk with 95% confidence interval will be used to analyse treatment effect according to intention-to-treat. Analysis of binary secondary outcome measures will be performed similar to the primary outcome (such as perineal hernia rate, re-intervention rate, wound complication etc.). All *p*-values will be two-tailed and a p-value of < 0.05 will be considered statistically significant. Subgroup analyses will employ a test of interaction to explore whether there is evidence that the treatment effects differ across subgroups. As with all subgroup analyses these will be interpreted with caution, and will be considered hypothesis generating.

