## Methods/design

### Objective

The objective of this study is to investigate the effect of gluteal turnover flap closure of the perineal wound with primary closure of the perineal wound after APR for rectal cancer. The hypothesis is that gluteal turnover flap reconstruction increases the uncomplicated perineal wound healing rate, and decreases the occurrence of perineal hernia.

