#### Secondary endpoints

Secondary endpoints are perineal wound healing according to the Southampton wound grading at 14 days, 3, 6 and 12 months postoperatively; postoperative pain score, the effect of neo-adjuvant treatment on perineal wound healing, incidence of persistent perineal or presacral sinuses both clinically and by imaging (routine follow-up CT), need for re-intervention or re-admission related to perineal wound problems, incidence of symptomatic and asymptomatic perineal hernia during follow-up, length of hospital stay, and quality of life and urogenital function (EQ-5D, EORTC-30, EORTC-29, SF36, UDI-6, IIQ-7, IIEF, FSFI, FSDS-R).

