### Sample size calculation

The proportions of patients with uncomplicated perineal wound healing between both study arms will be compared and analysed by the intention-to-treat approach. The hypothesis is that gluteal turnover flap closure increases the uncomplicated perineal wound healing rate compared to primary closure of the perineum.

Our recently conducted pilot study showed promising results of the gluteal turnover flap with a flap failure in zero of ten patients included, and no Clavien-Dindo complications of three or higher within 30 days of surgery. Among the ten patients, there were four minor complications and no major wound complications requiring re-intervention at 30 days postoperatively. The minor complications consisted of two perineal wound dehiscences, one perineal infection necessitating manual drainage and antibiotic therapy, and one non-infected perineal seroma that also required manual drainage. A recent published case series of 13 patients undergoing an APR for rectal cancer with a similar flap procedure showed no cases of flap loss and no donor site or major perineal morbidity [8]. Combining the outcome of our pilot study with the recently published case series results in an uncomplicated wound healing rate of 83% (19/23). In current literature an increase of uncomplicated perineal wound healing of approximately 20% is to be expected when a muscle flap is being used. However, these data are mostly derived from cohort series in which different kinds of flaps were being used, with different definitions of complicated perineal wound healing. Therefore the currently available literature is difficult to interpret with regard to perineal wound healing. In our previously conducted randomised controlled trial (the BIOPEX-study), there was an uncomplicated perineal wound healing percentage of 66% after primary perineal wound closure. Extrapolating the reported improvement in perineal wound healing, a total number of 146 patients (73 per group) are needed to be able to detect a 20% increase in primary perineal wound healing by use of a gluteal turnover flap (from 65 to 85%), applying a Chi-Square test with a two-sided 0.05 significance level and with 80% power. With an estimated drop-out of 10%, a total number of 160 patients are required (80 per group).

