### Data analysis

#### Primary endpoint

An intention-to-treat analysis will be performed on the primary outcome using a two-sided Chi-square test to compare the two study groups. A *p-*value of < 0.05 is considered statistically significant. Specific wound complications will be compared between the groups as categorical variables using the Mann-Whitney U test. A Kaplan-Meier survival analysis will be used to analyse the differences in time to perineal wound healing between the two study groups. Statistical analyses will be performed using SPSS software for Windows version 26.

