The perineal dead space after APR is often relatively limited and does not routinely require a large bulky tissue flap. A flap should therefore be relatively simple to perform, requiring only limited additional operative time, should be able to be combined with laparoscopic surgery and performed in both prone and supine positions, and should not add additional scars. The gluteal turnover flap, which constitutes the experimental intervention in the present trial, is a modified perforator flap which fulfils these criteria [8]. The gluteal turnover flap seems to be a promising method for the purpose of routine perineal closure after APR for primary and recurrent rectal cancer that does not require exenterative procedures. In addition to its positive effect on the perineal wound healing, it is expected that perineal hernia incidence will be reduced, by anchoring the strong dermis onto the contralateral remnant of the levator ani.

The use of neo-adjuvant therapy in the Netherlands has been reduced in the last couple of years. Therefore, non-radiated patient are also considered eligible in the BIOPEX-2, while only radiated patients were included in the BIOPEX trial. Neo-adjuvant therapy is one of the most import risk factors for perineal wound complications, and stratification will be used to balance the study arms for this factor.

It was decided to use the same control intervention in the BIOPEX-2 trial as used in the BIOPEX trial, namely primary perineal closure. The main reason was because no superiority of biomesh closure on the primary endpoint could be demonstrated. Although a significant difference in perineal hernia rate was found for the experimental arm in the BIOPEX study as a secondary finding, biological mesh closure did not become the standard of care in the Netherlands. The relatively high costs and relatively small absolute difference in perineal hernia rate were the main reasons for continuing primary closure as routine daily care in most Dutch institutions. Furthermore, the reduced perineal hernia rate needs further confirmation by long-term follow-up.

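### Hernia reduction is part of the stated hypothesis, yet it and every other secondary endpoint may be called significant at p < 0.05 whatever the primary result

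*Protocol article*

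**What the plan says.** The article names one primary endpoint, uncomplicated perineal wound healing at 30 days. Under Data analysis, Primary endpoint, it is tested with the rule "A *p-*value of < 0.05 is considered statistically significant".

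The hypothesis is stated twice, and the two statements differ. The Objective says that "gluteal turnover flap reconstruction increases the uncomplicated perineal wound healing rate, and decreases the occurrence of perineal hernia". The Sample size calculation restates the hypothesis for wound healing only, and only that endpoint is powered.

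Hernia appears under Outcome parameters, Secondary endpoints, as "incidence of symptomatic and asymptomatic perineal hernia during follow-up". It stands beside the wound score at four other times, pain, sinus, re-intervention or re-admission, length of stay and nine questionnaires.

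For these, Data analysis, Secondary endpoints, fixes one rule: "All *p*-values will be two-tailed and a p-value of < 0.05 will be considered statistically significant". The same paragraph calls subgroup analyses hypothesis-generating. No such label, testing order or link to the primary result is attached to the secondary endpoints.

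**The concern.** The article does more than stay silent on multiplicity. It fixes a rule for the secondary endpoints, and it limits interpretation for one class of analysis only. A reader who follows the text would call a hernia result with p < 0.05 significant without qualification. Because the Objective makes hernia part of the hypothesis, that result would look like support for the hypothesis even after a failed primary.

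The situation is not remote. According to the Background, the earlier trial found no benefit on wound healing but a lower hernia rate at one year (13% versus 27%, P = 0.0316). What is at stake is how much weight a similar pattern would carry here, and whether the plan settles that before the data are seen.

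**Working it through.** **1. The plan's own figure.** Inputs from the Sample size calculation: 65% versus 85%, "applying a Chi-Square test with a two-sided 0.05 significance level and with 80% power". With pooled variance and no continuity correction, the number per group is

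n = [1.960 × √(2 × 0.75 × 0.25) + 0.842 × √(0.65 × 0.35 + 0.85 × 0.15)]² / 0.20² = (1.200 + 0.501)² / 0.04 ≈ 72.4, rounded up to 73.

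This matches "a total number of 146 patients (73 per group) are needed". The full 0.05 is spent on healing, and hernia plays no part in the calculation.

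**2. The two-part hypothesis.** Take both nulls as true, with each test two-sided at 0.05. If the tests are independent, the chance of at least one false claim is 1 − 0.95² = 9.75%. For two-sided normal tests, independence is the worst case. At a correlation of 0.5 the figure is 9.1%, and at 0.8 it is 7.8%.

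**3. The secondary family.** The documents give no number of tests, so a count must be assumed.
- Clinical items: wound score at 14 days and 3, 6 and 12 months (4), pain, sinus, re-intervention or re-admission as the single item listed, hernia, and length of stay. Total 9. The neo-adjuvant effect is left out.
- Questionnaires: one test each. Total 9.
- Together 18. Counting re-intervention and re-admission separately and adding time to healing gives 20.

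Under independence the rate is 1 − 0.95^k. Under a common correlation ρ it is

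1 − ∫ [Φ((1.96 − √ρ·u)/√(1−ρ)) − Φ((−1.96 − √ρ·u)/√(1−ρ))]^k φ(u) du.

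| Tests k | ρ = 0 | ρ = 0.5 | ρ = 0.8 | ρ = 0.9 |
|---|---|---|---|---|
| 2 (healing, hernia) | 9.75% | 9.1% | 7.8% | 7.0% |
| 18 secondary | 60.3% | 39.8% | 21.6% | 15.1% |
| 20 secondary | 64.2% | 41.9% | 22.4% | 15.5% |

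Separate tests of questionnaire domains, which the Quality of life section says will be presented, would raise the last two rows.

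**4. Two ways to protect the hernia claim.** With a fixed sequence, hernia is tested at 0.05 only if healing is significant at 0.05. If both nulls hold, a false claim first requires a false primary result, so the rate is 5%. If healing truly improves, the hernia test has its own 5%. The 146 and 160 stay as they are. Splitting alpha instead, with 0.025 for healing, would need 88 per group, or would leave 71% power at 73 per group.

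**The case against.** The case on the other side is substantial.

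- *There is a hierarchy.* One primary endpoint is named, hernia is listed as secondary, and the powered hypothesis is healing alone. This stands. A reader might infer that the trial's main claim has an inflated error rate. It does not: the day-30 test keeps its 5%.
- *Several times 5% does not describe healing plus hernia.* This stands. The inflation there is below twofold. The larger figures arise only when all secondary comparisons are pooled, and nobody has proposed that pool as one claim.
- *The large figures rest on choices.* This stands. The count, the common correlation and the global null are assumptions, and the range is wide.
- *The hypothesis joins its two parts with "and".* If both had to be significant for any claim, the error rate would not exceed 5%. The article does not say so, and its rule allows each p-value to be declared on its own.
- *The Discussion concedes the problem.* A reader might take "the reduced perineal hernia rate needs further confirmation by long-term follow-up" that way. It concerns long-term follow-up of the earlier trial's result, not multiple testing, and is no evidence for this point.
- *Ordering of secondary endpoints belongs in an analysis plan.* Absence alone would indeed be no finding, and no sentence says that a significant secondary result will be reported as confirmed. What remains is a rule stated without qualification, next to two hypothesis statements that disagree on hernia.

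**Conclusion.** The point holds in a limited form. The primary inference is sound and the sample size reproduces. The defect is that the Objective and the Sample size calculation disagree on whether hernia belongs to the hypothesis, while the rule for secondary endpoints lets a hernia result be declared significant whatever happens to the primary.

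Its size for the two-part hypothesis is about 9%, at most 9.75%, against a nominal 5%, if either part may be claimed alone and neither effect exists. For the wider secondary family the chance of at least one false significant result is well above 5% even under strong correlation. The exact value is illustrative and should not be quoted as the trial's false-positive rate. This is a cheap improvement in what the trial may conclude.

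**What to change.** 1. Reconcile the Objective with the Sample size calculation, so that both say whether hernia is part of the hypothesis and with what standing.
2. In Data analysis, Secondary endpoints, name one key secondary endpoint: any perineal hernia, symptomatic or asymptomatic, by 12 months. Test it at two-sided 0.05 only if the day-30 primary test is significant. Naming one form also removes doubt about which hernia count decides the question.
3. State that all other secondary, time-to-healing and questionnaire comparisons are exploratory, reported as estimates with 95% confidence intervals and without confirmatory claims of significance. The section already plans relative risks with 95% confidence intervals, so this mainly extends to them the caution now given to subgroups.

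The cost is a few sentences in the protocol or analysis plan, before the data are unblinded. No patients or data are added, no alpha is taken from the primary test, and 146/160 is unchanged. The downside is that a hernia difference is only hypothesis-generating if the primary fails, and other secondary results can no longer be headlined as significant.

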#### Quality of life and urogenital function

Graphic representation will be used to portray quality of life and urogenital function data (EQ-5D, EORTC-30, EORTC-29, SF36, UDI-6, IIQ-7, IIEF, FSFI, FSDS-R) across all follow-up moments, analysed according to the manuals, and will presented as domain and summarised scores. Questionnaire outcome comparisons will be analysed using linear mixed models. All analyses will be according to the intention-to-treat principle.

### Data monitoring

An independent Data Safety Monitoring Board (DSMB) committee has been established to perform ongoing safety surveillance and interim analyses on the safety data. The DSMB is composed of two independent clinicians and one independent epidemiologist. None of the members has conflict of interest with the sponsor of the study. An interim analysis will be performed at 80 included patients (of the total of 160 patients). The steering committee will be supplied with the number of (serious) adverse events in both groups. If there is a skewed distribution of the number of (serious) adverse events between the two groups, an efficacy analysis can be performed at the discretion of the steering committee. Following these interim analyses, the steering committee will advise upon continuation of the trial.

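### The article permits a discretionary efficacy look at half enrolment with no stated limit on what it can conclude, so the overall 5% type I error is not guaranteed

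*Protocol article*

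**What the plan says.** **Interim analysis (Protocol article, Data monitoring).** One interim analysis is planned at 80 of 160 included patients. The section first describes a DSMB of two independent clinicians and one independent epidemiologist, whose interim analyses concern safety data. It then says that the steering committee receives the (serious) adverse-event counts for both groups. If these are skewed, a term the section does not define, "an efficacy analysis can be performed at the discretion of the steering committee". The consequence is: "Following these interim analyses, the steering committee will advise upon continuation of the trial".

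**Final analysis (Data analysis, Primary endpoint).** The primary outcome is analysed by intention to treat "using a two-sided Chi-square test to compare the two study groups". The significance rule is a p-"value of < 0.05 is considered statistically significant".

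**Sample size calculation.** The trial is sized "applying a Chi-Square test with a two-sided 0.05 significance level and with 80% power", and "a total number of 146 patients (73 per group) are needed".

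No other significance level for the primary outcome appears in the article. There is no interim boundary, no alpha allocation, and no statement that the trial cannot stop for efficacy.

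**The concern.** A comparison on the primary endpoint halfway through, whose result bears on continuation, is a second chance to reach a conclusion. If that chance may end in a claim of benefit, the probability of a false claim belongs to the two looks together. The article assigns all of the 0.05 to the second look and says nothing about the first.

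Two features make this more than a missing detail.

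- **The trigger is undefined and may be related to efficacy.** The Sample size calculation section treats wound dehiscence, perineal infection and seroma in the pilot study as complications, and its 19/23 healing rate excludes them. If such events also count as adverse events, an uneven split partly reflects a difference in the primary endpoint. The look would then tend to occur when the interim difference is large by chance. This is a plausible inference; the article does not say which events count.
- **Responsibility is inconsistent within the section.** The DSMB's interim analyses are described as being on safety data, yet the between-arm counts and the decision to look at efficacy go to the steering committee.

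At stake is the error rate behind the superiority claim. Stopping early on a favourable difference would also tend to overestimate the effect.

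**Working it through.** **1. The plan's own figure.** Inputs from Sample size calculation: 65% versus 85%, two-sided 0.05, 80% power, chi-square test. With pooled variance, no continuity correction and mean proportion 0.75:

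n per arm = [1.960 × √(2 × 0.75 × 0.25) + 0.842 × √(0.65 × 0.35 + 0.85 × 0.15)]² / 0.20²
= (1.200 + 0.501)² / 0.04 = 2.896 / 0.04 = 72.4, rounded up to 73.

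This reproduces 73 per group and 146 in total (power 80.3%). The calculation uses the full 0.05, so no alpha was set aside for an interim look.

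**2. Look always made, both looks at p < 0.05 (the interim threshold is an assumption).** Information fraction t = 80/160 = 0.5. The two test statistics are approximately bivariate normal with correlation √0.5 = 0.707.

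Overall error = 1 − P(|Z₁| < 1.96 and |Z₂| < 1.96) = 0.083.

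Binomial simulation of the chi-square test, with common healing rates of 65% to 85%, gives 0.082 to 0.086. If some 30-day outcomes are still pending at 80 included patients and t is 0.40 to 0.45, the normal calculation gives 0.086 to 0.085. In the same simulations the final test alone rejects in 4.8% to 5.2% of null trials.

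**3. Look made only when triggered.** If the trigger is independent of efficacy and has probability q:

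Overall error = 0.05 + q × (0.083 − 0.05) = 0.05 + 0.033q.

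This gives 0.053 at q = 0.10, 0.058 at q = 0.25 and 0.067 at q = 0.50.

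If the trigger is related to efficacy, a null simulation gives the results below. It uses 40 per arm at the interim and 80 at the end. Assumptions not in the article: every wound failure counts as an adverse event, 25% to 35% of patients fail, there are 0.3 other events per patient, and the interim test is at p < 0.05.

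| Trigger: adverse-event imbalance | Null trials in which the look occurs | Overall error |
|---|---|---|
| \|z\| > 0.5 | about 59% | 7.8–8.0% |
| \|z\| > 1.0 | about 26–28% | 7.3–7.4% |
| \|z\| > 1.5 | about 10–11% | 6.4–6.5% |
| \|z\| > 1.96 | about 3–4% | 5.7–5.8% |
| \|z\| > 2.58 | under 1% | 5.2–5.3% |

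**4. Strict interim boundary.** With an interim threshold of p < 0.001 (|Z₁| > 3.29) and the final test at 0.05:

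Overall error = 1 − P(|Z₁| < 3.29 and |Z₂| < 1.96) = 0.0502.

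For comparison, O'Brien-Fleming at t = 0.5 uses 0.0052 at the interim and 0.0480 at the end, which raises 146 to about 148.

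**5. No claim of benefit at the interim.** If the look can stop the trial only for harm or futility, efficacy can be claimed only at the final test. In simulation, with a stop when Z₁ < −1.96, claims favouring the flap occur in 2.4% to 2.6% of null trials, about the nominal 2.5% for that direction.

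**The case against.** A reader might infer that the trial will declare the flap effective at 80 patients if p < 0.05. The article does not say so. The 0.05 rule is stated for the primary analysis. The interim paragraph gives no threshold and mentions no early superiority claim; its only stated consequence is advice on continuation. The look sits in a safety paragraph and follows from an adverse-event imbalance, so a benefit-risk check on a safety signal is a natural reading. Used only in that way, it inflates nothing. This stands, and it means that 8.3% is the result of an assumed rule and not a property of the written plan.

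A reader might also infer that the final test itself fails to hold 5%. It does not; only the procedure as a whole can exceed it, and only through an early efficacy conclusion.

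The size is open too. A look that is always made does not match a conditional trigger, and |z| > 0.5, met in about 59% of null trials, would hardly be called skewed. With stricter triggers the excess falls below one percentage point.

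Finally, a boundary may exist in the full protocol, an SAP or a DSMB charter, and a final test at 0.05 is compatible with a very strict one. That weakens any complaint about absence alone. It does not dispose of what the article itself fixes: a discretionary efficacy look on an undefined trigger, assigned to the steering committee, with the result bearing on continuation.

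**Conclusion.** The concern holds in a limited form. The rule as published leaves open an early efficacy conclusion and sets no limit on it, while the full 0.05 is used at the end. The overall 5% error rate is therefore not guaranteed.

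No single inflation figure follows from the article, because neither trigger nor interim threshold is defined. The plausible range runs from no inflation (look used only for harm or futility), through about 5.2% to 8.0% (triggered look), to about 8.3% (look always made at half information). Both inflated figures assume that an interim p < 0.05 could support a claim. The triggered range also depends on the chosen cut-off, on wound failures counting as adverse events and on the assumed 0.3 other events per patient.

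The split of roles between DSMB and steering committee needs reconciling whichever reading is right. Because the look is optional and its stated consequence is advice, this is a point that should be fixed; the article does not demonstrate a failure of the primary analysis.

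**What to change.** Replace the sentence on the efficacy analysis with one of these two rules:

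- **(a) Safety only.** The interim analysis at 80 patients covers safety data, and no efficacy result can stop the trial for benefit. The final test stays at two-sided 0.05.
- **(b) Bounded look.** Any efficacy look is made by the independent DSMB. It can support an early efficacy claim only at two-sided p < 0.001 (Haybittle-Peto). The final test stays at 0.05, and the look is reported as planned whether or not it is triggered.

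Under either rule, state which body sees the between-arm adverse-event counts, so that the two descriptions in Data monitoring agree.

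**Cost.** One or two sentences in the protocol or SAP and the DSMB charter. No extra patients are needed: the final test is unchanged, so 73 per group still gives 80.3% power. The price is less scope to stop early for benefit.
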